**Summary**

Extensive experimental and observational data suggest that intake of both calcium and vitamin D exert protective effects on colorectal neoplasia. Building on our previous work, we will now investigate the chemopreventive effect of vitamin D in the large bowel, to study whether both agents together are more effective than calcium alone, and to confirm our positive finding regarding calcium. Our goal is the development of chemopreventive combinations that will reduce risk of colorectal neoplasia sufficiently to permit the lengthening of surveillance intervals in most patients and to clarify important issues regarding the mechanisms of colorectal carcinogenesis and chemoprevention.

***3.0 Summary of Study Plan***

*3.1 Overview*

This study is a double-blind, placebo-controlled trial of vitamin D and/or calcium supplementation for the prevention of large bowel adenomas. Subjects will be recruited from 11 Study Centers in North America. Eligible subjects will have had at least one large bowel adenoma removed in the 4 months prior to study entry and no remaining polyps in the bowel after complete colonoscopic examination. Participants will be randomized in a modified 2 x 2 factorial design to vitamin D (1000 IU/day), calcium carbonate (1200 mg elemental calcium/day), both agents, or placebo only. Women who decline to forego calcium supplementation will be randomized only to calcium alone or to calcium plus vitamin D. Randomization will be stratified by gender, Study Center of recruitment, and anticipated follow-up interval (see below), and will be conducted separately for female subjects randomized only to vitamin D. Participants will agree to avoid taking study agents outside the trial and will initially be observed in a 3-month placebo run-in period to identify (and exclude before randomization) subjects likely not to adhere to the study regimen. We anticipate enrolling about 3000 participants to reach a total of approximately 2400 randomized subjects. As safety measures, blood levels of calcium, creatinine and 25-(OH)-vitamin D will be obtained at baseline and 1 year after randomization, as well as 3 years after randomization for subjects with a 5-year surveillance cycle. Every six months after randomization subjects will complete a questionnaire regarding compliance with study agents, use of medications and vitamin/mineral supplements, illnesses, hospitalizations, and dietary intake of calcium and vitamin D.

The endpoint of the study will be new adenomas detected on follow-up colonoscopy. These examinations are scheduled to occur either 3 years or 5 years after the qualifying examination, depending on the follow-up interval recommended by each patient's endoscopist. Some patients may, for medical reasons, have a colonoscopy at a time other than 3 or 5 years after the qualifying examination. Information from these exams will be included in analyses where appropriate. In the primary analyses, the occurrence of new neoplastic polyps in the interval between randomization and the follow-up exam will be compared between subjects randomized to vitamin D (with or without calcium) versus those randomized to placebo (with or without calcium), between subjects randomized to calcium (with or without vitamin D) versus those randomized to placebo (with or without vitamin D, excluding women electing to receive calcium and therefore cannot participate in the calcium component of the study), and between those randomized to calcium plus vitamin D versus those randomized to calcium alone. In secondary analyses, we will examine the effect of calcium plus vitamin D versus vitamin D alone, and the impact of baseline vitamin D levels and VDR polymorphisms on the vitamin D effects. Effects on advanced adenomas will also be assessed.

*3.2 Schema*

# Colorectal Chemoprevention with Calcium and Vitamin D

# [name], Dartmouth Medical School

Men and women with a recent colonoscopy in which an adenoma was removed,

with acceptable baseline measurements of calcium, creatinine and 25-(OH)-vitamin D

Three month RUN-IN period (about 3000 participants)

Randomize about 2400 men and women to:

placebo (360 men and 84 women) or

1200 mg elemental calcium (360 men and 84 women) or

1000 IU vitamin D (360 men and 84 women) or

both agents (360 men and 84 women) daily

-OR-

Randomize women who want to take calcium to:

1200 mg elemental calcium (312 women) or

1200 mg elemental calcium and 1000 IU vitamin D (312 women) daily

Subject questionnaires at 6-month intervals

Measurements of calcium, creatinine and/or 25-(OH)-vitamin D at year 1, year 3 and, if applicable, year 5

Follow-up colonoscopy at 3 or 5 years

Number and type of new colorectal adenomas found

***4.0 Subject Selection and Enrollment***

*4.1 Study Population*

Study subjects will be healthy volunteers who have received preventive care from a gastroenterology clinic. They will be recruited to the study because they are at risk for future adenomas based on the occurrence of at least one previous adenoma removed at a surveillance colonoscopy (qualifying colonoscopy) occurring within the previous four months. Recruited subjects will be between 45 and 75 years of age at enrollment. Current preventive health care guidelines suggest an initial screening colonoscopy at 50 years of age. Individuals younger than 45 are excluded because adenomas occurring in that age group may be due to the presence of a familial colon cancer syndrome. Thus, they are likely to represent a different population with a different mechanism. The upper age limit for inclusion in the trial is used to increase the likelihood of successful compliance and completion of this long-term chemoprevention trial.

Individuals of both genders and all racial and ethnic populations will be encouraged to participate in the trial. Based on previous trials, we anticipate that approximately 60% of enrolled subjects will be males and 40% females. This accords with the demographics of adenoma prevalence, which is somewhat higher among men. We expect the ethnic and racial make-up of the subject population to approximate that of the U.S. population. The diversity of populations in the catchment areas of our 11 Study Centers makes this a realistic goal.

*4.2 Participating Study Centers and Recruitment Sites*

Subjects will be recruited from the gastrointestinal and surgical services of the eleven participating Study Centers. Principal Investigators (PI) for each Study Center are provided below. Recruitment or referral will also occur from ancillary sites, including hospitals, clinics, cancer centers, university medical practices, Veterans Affairs Medical Centers, health maintenance organizations, and private gastroenterology practices associated with these centers, as listed below. Those recruitment sites listed below that have an Institutional Review Board (IRB) that provides human subject’s oversight for this study that is separate from that of the Study Center are indicated with an asterisk.

1. Dartmouth Hitchcock Medical Center, Lebanon, NH

(PI: [name])

- 1. Dartmouth-Hitchcock Manchester, Manchester, NH
  2. Dartmouth-Hitchcock Keene, Keene, NH

- 1. Los Angeles County Hospital, Los Angeles, CA
  2. South Bay Gastroenterology Medical Group
  3. Kaiser/Sunset, Los Angeles, CA*

1. University of Texas, Houston, TX

(PI: [name])

- 1. MD Anderson Cancer Center, Houston, TX
  2. Medical Center Endoscopy, Houston, TX

11. University of Puerto Rico, San Juan, PR

(PI: [name], PhD)

- 1. VA Caribbean Healthcare System, San Juan, PR*
  2. Active GI Group, San Juan, PR
  3. Instituto de Gastroenterología, San Juan, PR
  4. Hato Rey Medical Gastroenterology, Hato Rey, PR

e. Grupo Gastroenterologico del Este, Humacao PR

*4.3 Sources and Methods of Recruitment*

Study coordinators or treating medical staff will identify potential subjects through review of colonoscopy schedules and pathology reports at the participating centers and associated practices. All potential subjects must have had at least one adenoma that is at least 2 mm in size removed from the large bowel in the four months before entry into the study. For these diagnoses, we will accept the readings of the local pathologists. For individuals who meet this initial criterion, a preliminary determination of eligibility will then be made through review of available medical records and contact with the participating physicians. Those individuals who continue to be eligible following this review will be assigned a study ID number for tracking and reporting purposes upon submission of preliminary eligibility data to the Dartmouth Project Coordination Center. This eligibility data will include the individual’s date of birth and the date of the qualifying colonoscopy exam (components of a limited data set as defined by HIPAA) as permitted by local regulatory requirements.

Study Centers will implement the following process as permitted/required by local IRBs: Potential subjects will be mailed a packet of information about the study, preferably from their personal physician or clinical staff with whom they are familiar. This packet (packet #1) will include:

Introductory letter with a short description of the study and the name of the study coordinator who will be contacting the patient to determine their interest in participation.

Post card that may be returned to decline further contact regarding the study or to provide information about a good time to reach them by phone

Study brochure describing the study in more detail

Medical release authorization (may be required to verify eligibility)

The study coordinator will phone those individuals who do not decline further contact within 14 days to discuss their interest in the study, to confirm eligibility and to set up an intake appointment for those individuals who are interested in study participation. A second information packet (packet #2) will be mailed to these individuals containing:

- Letter confirming the intake appointment date and time
- Checklist of what to bring to the intake appointment
- Block Food Frequency questionnaire
- RAND SF-36 Health Survey
- Copy of the study’s Informed Consent document

Brochure from the NIH/NCI called “Taking Part in Clinical Trials: Cancer Prevention Studies – What Participants Need to Know “ or brochure from The Office for Human Research Protections called “Becoming a Research Volunteer: It's Your Decision”

*4.4 Enrollment Procedures*

An intake appointment will be scheduled within 120 days of the qualifying colonoscopy for those individuals who continue to be interested in study participation. At the intake appointment, an informed consent discussion will take place between the prospective participant and the study coordinator. After obtaining signed consent (the date of the signed consent is the Enrollment Date for the participant), the study coordinator will confirm eligibility and document the subject’s general demographic information, general health and medical history including previous colorectal procedures and adenomas, use of nutritional supplements and medications, recent sun exposure and exercise, smoking history, and family history of cancer or adenomas (the Intake Questionnaire). The responses to these questions will be entered by the study coordinator into a secure web-based form that transmits data directly to the Dartmouth Project Coordination Center in real-time over the Internet. The participant will also be asked to complete and submit to the study coordinator a Block Food Frequency Questionnaire and an SF-36 Health Survey. The Block Food Frequency Questionnaire is a validated self-administered questionnaire that is intended for epidemiologic and clinical use and captures an individual’s usual dietary food intake. The SF-36 Health Survey is a validated 36-item self-administered questionnaire on health status that assesses eight different health concepts and includes perceptions of both physical and mental health.

In a final component of the intake appointment, the study coordinator will measure and document the participant’s current height and weight, and obtain the baseline blood draw. Whenever possible, this should be a fasting blood draw (the participant should not eat food or drink beverages other than water for 8 hours prior to the blood draw). Regardless, the time of the last food or beverage intake will be collected. Pre-packaged bar-coded blood collection kits will be provided for each participant. Standard and detailed operating procedures will be provided by the Dartmouth Project Coordination Center for adequate and safe collection, processing, storage and shipment of these biospecimens.

Upon completion of the intake appointment, all participants will be given a study packet (packet #3) containing:

- Copy of the signed and dated informed consent form
- Participant Information Booklet
- Phone card -optional (Additional phone cards will be sent or given to subjects from the Study Center on a yearly basis.)
- 7-day pill dispenser
- Bottle of run-in study pills
- Study Identification Card
- Bottle of multivitamins without any vitamin D or calcium -optional per subject request (Additional bottles will be sent or given to subjects from the Study Center as needed.)
- Participant Drug Information Card (optional per local IRB requirement)

The study coordinator will ask the participant to take the first study pill. The coordinator will document the taking of the first pill at the intake appointment or ask the participant to confirm by postcard or telephone if taken later. All prospective participants who complete the intake appointment will be reimbursed $100 to defray the time and expense of the recruitment/enrollment activities.

The study coordinator will ship blood samples for Vitamin D measurements to the UCLA Nutrition Research Center at the next scheduled shipment date. (The UCLA laboratory will provide the results of these measurements directly to the Project Coordination Center.) In addition, within 15 days after the intake appointment, the study coordinator will submit to the Dartmouth Project Coordination Center the qualifying pathology and endoscopy reports and the results of the local lab measurements of calcium and creatinine. These lab results and clinical reports will be required to confirm the eligibility of the participant prior to randomization. If the results for calcium or creatinine are outside of the range for eligibility (see section 4.7 below) then the subject and their health care provider will be notified of the result in writing. If the result for 25-(OH)- vitamin D is outside of the range for eligibility (see section 4.7 below), then the subject and their health care provider will be notified in writing whether the result is “too high” or “too low.” The exact measurement will not be provided because these study measurements are not performed in a CLIA certified lab and so can be used for research purposes only. The health care providers for the affected subjects will be advised to obtain a 25-(OH)- vitamin D level at a CLIA-approved laboratory if further assessment is thought to be indicated.

Other information to be sent to the Project Coordination Center includes the completed Food Frequency Questionnaire, which will be mailed, and the SF-36 Health Survey, which will be mailed until the web form is available for data entry and transmission over the internet. These must be received by the Project Coordination Center within 60 days of the intake appointment. Finally, with the consent of the participant, the coordinator will also ship (within 60 days of the intake appointment) blood samples to the Clinical & Molecular Pharmacology Shared Resource of the Norris Cotton Cancer Center to be stored for future research on colorectal neoplasia and other disorders common in the study population.

Quality Control. The Dartmouth Project Coordination Center will review the pathology and endoscopy reports to confirm the Study Center’s assessment of eligibility before the prospective participant is randomized.

*4.5 Run-in period and randomization assessment*

At the intake appointment, or immediately upon taking the first run-in pill, the participants will enter an approximately three month long run-in period during which adherence to study agents will be assessed. Approximately 10 weeks after the intake appointment, the study coordinator will contact participants by phone to determine and document continued interest in the study, any change in eligibility or exclusionary criteria, and run-in pill taking compliance. Subjects will be asked to count the number of pills left in their pill bottles and report this number to their study coordinator who will enter it into a web form that will be used to calculate compliance. Participants whose pill counts indicate that they have taken less than 80% of their study pills will not be randomized. Participants will also be given their first ‘interval’ questionnaire on this phone call (see section 6.1 below). This phone call must occur between 56 and 84 days of the intake appointment. After this phone call, participants who continue to be eligible for and interested in study participation will be sent a new supply of study pills by mail from the Dartmouth Project Coordination Center. The new supply will be the randomly assigned study agent. Participants will be provided a postcard or telephone number to report the date the first pill was taken from this shipment. It should be taken within 98 days of the intake appointment. Study coordinators will follow-up to collect this date if the patient forgets to report it.

*4.6 Method of Subject Identification*

All potentially eligible individuals identified by a review of colonoscopy and pathology records will be assigned a study identification number prior to initial patient contact. The ID number will be in the form SC - RS - ##### . The “SC” is a number ranging from 01-99 and identifies the Study Center from which the subject was recruited. The “RS” is a number ranging from 01- 99 and corresponds to the specific recruitment site. The “#####” ranges from 00001-99999 and identifies the individual subject. This number is generated using a modulo 11 method that prevents the occurrence of sequential numbers in order to reduce errors from typing mistakes. If an individual is subsequently enrolled in the study then this same ID number will be used throughout the study. In addition, upon enrollment the subject will also be assigned a two letter study identification code consisting of the first initial of the subject’s first name followed by the last letter of the subject’s last name. This code will be used along with the subject’s study ID number in communications between the Dartmouth Project Coordination Center and the Study Center coordinators.

*4.7 Inclusion criteria*

1. One or more histologically verified neoplastic polyp (adenoma) that is at least 2 mm in size removed from the large bowel with the entire large bowel examined by colonoscopy and documented to be free of further polyps or areas suspicious for neoplasia within 120 days of study entry
2. Anticipated colonoscopic follow-up three years or five years after the qualifying colonoscopy
3. Age between 45 and 75 years at enrollment
4. (Women)Agreement to avoid pregnancy (i.e. use of standard contraception)
5. Willingness to forego calcium supplementation (including multivitamins containing calcium) or, for women only, option of taking calcium supplementation of 1200 mg/daily (contained in the study pills)
6. Willingness to forego vitamin D supplementation (including multivitamins containing vitamin D)
7. Agreement to daily dietary intake of the equivalent of not more than 1200 mg calcium
8. Agreement to daily dietary intake of the equivalent of not more than 400 IU vitamin D
9. Blood calcium level within normal range
10. Blood creatinine level not to exceed 20% above upper limit of normal
11. Serum 25-(OH)-vitamin D within lower limit of 12 ng/ml to upper limit of 90 ng/ml

12) Ability and willingness to follow the study protocol, as indicated by provision of informed consent to participate

13) Good general health, with no severely debilitating diseases or active malignancy that might compromise the patient's ability to complete the study

*4.8 Exclusion criteria*

(General exclusionary criteria:)

1. Participation in another colorectal (bowel) study (intervention study) in the past 5 years
2. Current participation in any other clinical trial (intervention study)
3. Pregnancy or lactation
4. A diagnosis of narcotic or alcohol dependence in the past 5 years
5. A diagnosis of dementia (e.g. Alzheimers) in the past 5 years
6. A diagnosis of a significant psychiatric disability (e.g. Schizophrenia, refractory bipolar disorder, current severe depression) in the past 5 years

(Exclusions due to derangement of calcium metabolism or indications/contraindications to study agents)

1. Any diagnosis of kidney stones
2. A diagnosis of granulomatous diseases, e.g. sarcoidosis, active chronic fungal or mycobacterial infections (tuberculosis, histoplasmosis, coccidioidomycosis, blastomycosis), Berylliosis, Wegener’s granulomatosis in the past 5 years
3. A diagnosis of hyperparathyroidism or other serious disturbance of calcium metabolism in the past 5 years
4. A diagnosis of severe kidney disease, e.g. chronic renal failure in the past 5 years
5. A diagnosis of unexplained hypercalcemia in the past 5 years
6. Any diagnosis of osteoporosis with physician recommendation for treatment of low bone mass
7. A diagnosis of two or more low trauma fractures in the past 5 years
8. A diagnosis of a medical condition requiring treatment with vitamin D (e.g. osteomalacia) in the past 5 years

(Exclusions due to intestinal or bowel problems:)

1. Any diagnosis of invasive carcinoma of the large bowel (even if confined to a polyp)
2. Any diagnosis of familial colorectal cancer syndromes, e.g. Familial Adenomatous Polyposis (FAP) (including Gardner syndrome, Turcot’s syndrome), Hereditary Nonpolyposis Colorectal Cancer (HNPCC), Hamartomatous Polyposis syndromes (including Peutz-Jeghers or Familial Juvenile Polyposis)
3. Any diagnosis of inflammatory bowel disease, e.g. Crohn’s Disease, Ulcerative Colitis
4. A diagnosis of chronic intestinal malabsorption syndromes, e.g. celiac sprue, bacterial overgrowth, chronic pancreatitis, pancreatic insufficiency in the past 5 years
5. Any large bowel resection

(Exclusions due to poor health:)

1. A diagnosis of malignancy, other than non-melanoma skin cancer in the past 5 years
2. A diagnosis of severe lung disease – class 3 or 4 (e.g. COPD or emphysema requiring oxygen) in the past 5 years
3. A diagnosis of severe heart disease: Cardiovascular disease functional class 3 or 4 in the past 5 years
4. Any diagnosis of severe liver disease, e.g. Cirrhosis

(Exclusions due to shipping regulations:)

1. Any current/past HIV positive diagnosis
2. Active hepatitis B, defined as : Hep B surface antigen positive

Active hepatitis C, defined as : measurable HCV RNA

(Drug exclusions:)

1. Use of chronic oral cortico-steroid therapy in the past 5 years
2. Use of Lithium in the past 5 years
3. Use of Phenytoins in the past 5 years
4. Use of Quinidine in the past 5 years
5. Use of therapeutic vitamin D in the past 5 years

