Calcium supplementation is widely used and is safe. The Institute of Medicine’s recommended calcium intake for adults 19 through 50 years old is 1000 mg/day, for adults 51 through 70 years it is1200 mg/day for women and 1000 mg/day for men, and for those over 70 years it is 1200 mg/day.[94](#_ENREF_94) Intake up to 2000 mg/day in adults over 50 is considered safe.[94](#_ENREF_94) The main potential toxicities of calcium supplementation are urinary stones and hypercalcemia (which can lead to renal insufficiency and alkalosis, the “milk-alkali syndrome”). We will exclude from our study all subjects with renal insufficiency or a history of kidney stones. Milk alkali syndrome is rare in healthy people, and has not been noted in trials of calcium and vitamin D supplementation that used doses similar to those we propose.

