***5.0 Agent Information and Administration***

- 1. *Name of agents and study arms*

There will be four arms in the study:

1. placebo
2. calcium carbonate (3 gm/daily; 1200 mg elemental calcium/daily)
3. vitamin D3 (1000 IU/daily)
4. calcium carbonate and vitamin D3

*5.2 Assignment and Duration of Study Treatment*

Men will be randomly assigned to each of the treatment groups at equal frequency. Due to recommendations for high calcium intake among post-menopausal women and the common use of calcium supplements in that population group, women will have the option of being randomized to calcium or to calcium plus vitamin D (arm 2 or 4). In this way, they will receive 3 gm of supplemental calcium carbonate daily as part of the study. Based on our experience in the Aspirin-Folate Polyp Prevention Study, we assume that 35% of women will accept the full factorial randomization and 65% will wish to continue calcium supplementation and accept the restricted randomization (two arm). There will be separate randomization procedures for subjects being randomized to both agents and for women taking calcium who will be randomized only to vitamin D. Although it will not be encouraged, at any time after enrollment, women who are in the Full Factorial component of the study will have the option to change their mind and switch to the 2 Arm component of the study. Study tablets shipped to these subjects will be changed accordingly. For statistical analyses purposes they will be analyzed as per the original treatment group that they were randomized to. All randomization will be stratified by Study Center of recruitment and scheduled colonoscopic follow-up (3 years or 5 years).

The follow-up interval for colonoscopy recommended by a patient's endoscopist, either 3 or 5 years, will determine the duration of exposure to the study agents. For a 3 year follow-up interval, the duration of exposure to the study agents will be approximately two and one half years (30 months) due to the subtraction of the initial time required for subject identification and recruitment (up to four months) and a subsequent three month run-in period during which subjects take placebo pills (full factorial) or calcium alone (two arm). Likewise, the duration of exposure to the study agents will be approximately 4 and one half years (54 months) for a 5 year follow-up interval.

*5.3 Dose selection – safety and efficacy*

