Both agents have a considerable margin of safety in the doses to be used. The calcium dose of 1200 mg has been widely used; in our previous trial, this dose did not confer any toxicity. This dose is very likely to be effective. Our previous clinical trial results, together with human dietary epidemiology, indicate that the calcium dose will be associated with a decreased risk.

The vitamin D dose, 1000 IU daily, has been shown to be safe in intervention studies in humans. Together with the vitamin D in diet (typically 200-300 IU), the total vitamin D intake will be well below the 2000 IU dose set as the “no observed adverse effect level,” a standard that is itself conservative. This dose is also likely to be effective. Human epidemiological data suggest that doses of vitamin D in the range of high dietary intake or common supplemental doses may decrease the risk of colorectal neoplasia.

*5.4 Formulation*

We will use calcium carbonate for the calcium supplementation. This compound provides the convenience of supplying 1200 mg of elemental calcium in two tablets; other calcium salts would require a larger number of pills.

We will use vitamin D3 for the vitamin D supplementation. This will avoid the greater toxicity risks associated with 1,25-(OH)2 vitamin D or 25-OH vitamin D. This form of vitamin D is a pro-hormone that must be metabolized by normal mechanisms in the body to generate the most active moiety. Supplementation with even large doses of vitamin D3 does not increase total 1,25-(OH)2 vitamin D levels in individuals who are not vitamin D deficient, although toxicity may still ensue.

Each pill will contain either placebo or elemental calcium (600 mg) and either placebo or vitamin D (500 IU).

*5.5 Administration*

The study agents will be taken orally, twice a day, preferably with meals. Food increases the natural acidity of the stomach thereby enhancing calcium carbonate absorption.

*5.6 Side effects*

Calcium supplements are generally well tolerated. Use of calcium carbonate reportedly may cause such gastrointestinal side effects as bloating, gas and flatulence. Prolonged use of large doses of calcium carbonate –greater than 12 grams daily- may lead to the milk-alkali syndrome, nephrocalcinosis and renal insufficiency.

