- asking participants to report all medications being taken during study participation and advising them to consult with their physician about staggering the administration of current drugs or new medications that are begun during study participation.
- measuring calcium, creatinine and/or vitamin D levels approximately one year and, where applicable, three years after randomization; patients who have developed hypercalcemia, renal insufficiency or very high levels of 25-OH vitamin D (> 100 ng/ml) will be withdrawn from treatment.
- reviewing adverse events by blinded (and if necessary unblinded) treatment groups by the Safety and Data Monitoring Committee; this Committee will have overall responsibility for interpreting data on adverse events and recommending actions to ensure that subjects are not exposed to undue risks.

A physical risk that may be associated with insufficient intake of calcium or vitamin D over the long term is an increased risk for osteoporosis, a condition in which increased bone fragility can lead to fractures. This risk may be greater among post-menopausal women who undergo accelerated bone loss around the time of the menopause. The risk may be increased if subjects randomized to placebo reduce their dietary intake of calcium or vitamin D or stop taking calcium- or vitamin D-containing dietary supplements as a result of their participation in this trial. To protect against this risk:

- - Female subjects will be offered the option of being randomized to calcium alone or to calcium plus vitamin D. These women will receive 1200 mg of elemental calcium daily in their study pills.
  - Subjects will be cautioned NOT to reduce their dietary intake of calcium or vitamin D containing foods during their participation in this trial UNLESS we alert them that their intake is too high. Dietary intake will be assessed with a brief dietary screener at enrollment and randomization, and at six month intervals after randomization. Subjects will be counseled that dietary intake of calcium and vitamin D equivalent to about one quart of milk (about 1200 mg elemental calcium and 400 IU vitamin D) daily is acceptable for participation in this trial.

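### Accepted dietary calcium plus the study dose allows 2400 mg/day, 20% above the intake the protocol cites as safe, and the protocol never adds or reconciles the two

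*Protocol*

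**What the plan says.** **Diet.** Protocol section 4.7, criterion 7, requires "Agreement to daily dietary intake of the equivalent of not more than 1200 mg calcium". Section 14.2.1 carries the same level into follow-up: participants are told that a diet equivalent to roughly a quart of milk ("about 1200 mg elemental calcium and 400 IU vitamin D) daily is acceptable for participation in this trial"). They are also told not to cut back on dietary calcium unless the study alerts them that intake is too high.

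**Study dose.** Section 5.1 gives the calcium arm as "calcium carbonate (3 gm/daily; 1200 mg elemental calcium/daily". Section 5.4 states "Each pill will contain either placebo or elemental calcium (600 mg) and either placebo or vitamin D (500 IU", and section 5.5 states "The study agents will be taken orally, twice a day, preferably with meals". Criterion 5 rules out calcium supplements other than the study pills.

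**Cited safe intake.** The calcium chemoprevention text in section 2.0 lists recommended daily intakes and then says "Intake up to 2000 mg/day in adults over 50 is considered safe". Entry is open from a lower age: "Age between 45 and 75 years at enrollment" (section 4.7).

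**Margin of safety.** Section 5.3 opens with "Both agents have a considerable margin of safety in the doses to be used". For vitamin D it adds typical diet to the study dose and compares the total with 2000 IU. For calcium it refers only to the 1200 mg dose, its wide use and the group's previous trial.

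**The concern.** Study calcium comes on top of diet, so the quantity to set against a safe-intake figure is the sum. Two rules in the protocol, one for entry and one for continuing counselling, accept a diet that, with the study pills, takes a fully compliant participant past the only safe-intake figure the protocol cites for calcium. No section adds the two amounts or says why a higher total is acceptable.

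Section 2.0 names urinary stones and hypercalcaemia, the latter able to lead to renal insufficiency, as the main potential toxicities of calcium supplementation. Section 14.2.1 promises review of excess dietary or supplemental intake, with discontinuation when indicated, but puts no number on excess. The only benchmark it offers is the 1200 mg/day that it calls acceptable. A coordinator following the text therefore has no stated basis for regarding 2400 mg/day in total as a departure from anything.

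**Working it through.** **Inputs**

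| Quantity | Value | Protocol section |
|---|---|---|
| Accepted dietary calcium | 1200 mg/day | 4.7 (criterion 7); 14.2.1 |
| Elemental calcium per pill | 600 mg | 5.4 |
| Pills per day | 2 | 5.4, 5.5 |
| Cited safe intake, adults over 50 | 2000 mg/day | 2.0 |
| Age at entry | 45 to 75 | 4.7 |

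**Step 1: reproduce the stated dose.** 2 pills × 600 mg = 1200 mg/day, which matches section 5.1.

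**Step 2: permitted maximum on calcium.** Diet + dose = 1200 + 1200 = 2400 mg/day.

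**Step 3: compare with the cited figure.** 2400 − 2000 = 400 mg/day; 2400 / 2000 = 1.20, an excess of 20%.

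**Step 4: diet at which the cited figure is passed.** 2000 − 1200 = 800 mg/day. This is arithmetic, not a suggested threshold. For people over 50, section 2.0 gives recommended intakes of 1000 to 1200 mg/day. A calcium-arm participant who met those from diet alone would take 1000 + 1200 = 2200 to 1200 + 1200 = 2400 mg/day.

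**Step 5: the same check for vitamin D.** Section 5.3 uses a typical diet of 200 to 300 IU: 1000 + 200 to 1000 + 300 = 1200 to 1300 IU, below 2000 IU. At the 400 IU dietary ceiling of criterion 8 the total is 1400 IU, still below. Vitamin D therefore passes even at its permitted maximum; calcium at its permitted maximum does not.

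**Who is affected.** Only those receiving calcium: calcium alone, calcium plus vitamin D, both groups of the two-arm component, and the two-arm run-in, during which calcium is given. Placebo and vitamin D alone are unaffected.

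**The case against.** Several points on the other side are sound.

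- **Status of the 2000 mg figure.** It is background from a cited report. The trial does not adopt it as a cap, and the sentence does not say that more is unsafe. A reader might infer that the trial breaches its own safety limit. The text supports less than that: rules that permit more than the one figure the protocol offers as safe, without comment. Section 2.0 does not use the word total, but the sentence follows recommended-intake figures, so total intake is the natural reading.
- **Toxicity figure.** Section 5.6 links milk-alkali syndrome, nephrocalcinosis and renal insufficiency to prolonged use above 12 g of calcium carbonate daily. At the protocol's ratio (1200 / 3000 = 0.4) that is 4800 mg elemental; the study dose is a quarter of it and 2400 mg is half. The margin claim in section 5.3 is worded about doses. One therefore cannot say that the claim is false for these participants, only that it has not been tested against diet plus dose.
- **Unequal comparison.** For vitamin D the protocol used typical diet, not the ceiling. A like-for-like calcium check needs typical dietary calcium, which is not given. Step 5 meets this in part.
- **Ages 45 to 50.** With no upper intake cited for them, they cannot be shown to exceed one. The gap is an absent figure, not an excess.
- **Numbers exposed.** The schema in section 3.2 puts 2 × (360 + 84 + 312) = 1512 of 2400 (63%) on calcium. A reader might take this as the share above 2000 mg/day; it is only the planned size of the calcium arms.
- **The October 2011 Unanticipated Problem.** Sections 6.3.1 and 6.3.2 order creatinine testing and set criteria for stopping study calcium. A reader might infer that calcium caused the problem. Those sections state no cause and no link to dietary or total intake.
- **Safeguards.** There are renal, kidney-stone and hypercalcaemia exclusions (4.8), calcium and creatinine monitoring (6.3), and withdrawal rules and review of excess intake (14.2.1). These lower the risk. They do not remove the mismatch, because 1200 mg/day from diet is itself declared acceptable.
- **Timing.** Section 10.7 reports 2,813 enrolled and 2,259 randomised, so revising criterion 7 would reach no new entrant.

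**Conclusion.** The inconsistency stands. The protocol accepts up to 2400 mg/day of calcium in participants given study calcium, 400 mg (20%) above the intake it cites as safe in adults over 50. It cites no safe upper intake for eligible people aged 45 to 50. It makes no diet-plus-dose comparison for calcium while claiming a considerable margin for both agents.

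This rests on reading the 2000 mg/day as total intake, on full adherence to the pills, and on a diet at the accepted ceiling. How many participants pass 2000 mg/day is unknown, because no distribution of dietary calcium is given. The documents do not show that harm resulted or that an adopted limit was broken. The point is nevertheless relevant to safety and inexpensive to settle.

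**What to change.** The sponsor and safety committee should reconcile four places: the safe-intake sentence in section 2.0, criterion 7 in section 4.7, the margin statement in section 5.3, and the counselling text in section 14.2.1, including its undefined reference to excess intake. Either the accepted diet plus study dose should agree with the safe intake the protocol cites, or the protocol should state and justify the higher total. The position for ages 45 to 50 should be covered in the same text, and the calcium margin statement in section 5.3 corrected to match. Which figure applies is for the sponsor and the committee; none is proposed here, and no new eligibility or flagging rule is suggested.

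The cost is a protocol amendment, with matching changes to counselling material if the accepted diet changes. The dietary screener is already completed at enrolment, at randomisation and every six months, so no new data collection is needed. The likely price is a less favourable margin statement for calcium. With enrolment complete, the change would act through counselling and the six-monthly dietary review for participants still on treatment.
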